# WARRIOR-trial - is routine radiography following the 2-week initial follow-up in trauma patients with wrist and ankle fractures necessary: study protocol for a randomized controlled trial

**DOI:** 10.1186/s13063-015-0600-x

**Published:** 2015-02-27

**Keywords:** Wrist fracture, Distal radius fracture, Ankle fracture, Radiography, Functional outcome, Cost-effectiveness, Routine follow-up

## Abstract

**Background:**

Extremity fractures such as wrist and ankle fractures are a common and costly healthcare problem. The management of these fractures depends on fracture type and loss of congruity of the joint, resulting in cast immobilization or operative treatment. Loss of congruity or displacement leading to uneven joint loading, osteoarthritis and an increased probability of a poor functional outcome should be identified within the first 2 weeks post-trauma, based upon radiographs to determine optimal treatment. After this period, routine radiographs are scheduled for monitoring the bone-healing process. Current protocols describe imaging at 1, 2, 6 and 12 weeks post-trauma. However, it is questionable whether routine radiography following the initial follow-up ( 2-weeks post-trauma) is cost effective.

The aim of this study is to determine whether a modification of the radiographic follow-up protocol can be conducted with no worse outcome and less cost than the current standard of care for patients with a wrist or ankle fracture.

**Methods/design:**

In a multicenter randomized controlled trial, 697 patients aged 18 years or older will be included: 385 wrist fracture- and 312 ankle fracture patients. Patients will be randomized into two groups: Group 1 receives usual care, consisting of radiographs 1, 2, 6 and 12 weeks post-trauma; Group 2 receives radiographs beyond the initial follow-up only when clinically indicated. The primary outcome is the overall extremity-specific function. For wrist fractures, this includes the Disabilities of the Arm, Shoulder and Hand Score; for the ankle fractures, this includes the Olerud and Molander ankle score. Secondary outcomes include: healthcare cost, the specific function measured with the Patient Rated Wrist and Hand Evaluation for wrist fractures and American Academy of Orthopaedic Surgeons foot and ankle questionnaire for ankle fractures, pain-intensity, health-related quality of life, self-perceived recovery, and complications. Both groups will be monitored at 1, 2, and 6 weeks and 3, 6, and 12 months.

**Discussion:**

This study will provide data on (cost) effectiveness of routine radiography in the follow-up of wrist and ankle fractures, and could pave the way for a change in (inter)national protocols.

**Trial registration:**

Netherlands Trial Register NTR4610, registration date 22 June 2014.

## Background

Extremity fractures are a common and costly healthcare problem affecting all age groups [1]. In the adult population, the incidence of fractures to the wrist (distal radius) and ankle (malleolar fractures) in the Netherlands is about 20,000 and 15,000 per year, respectively [2]. These are the most common fractures encountered, accounting for about 18% and 10% of all fractures, respectively. Treatment of fractures consists of either immobilization or surgical fixation (18% of distal radius fractures and 35% of ankle fractures) [3]. The decision to operate should preferably be established within the first 2 weeks, as after this period the bone healing has advanced to a stage in which surgical treatment is more difficult. Loss of congruity or (secondary) displacement can lead to uneven joint loading, osteoarthritis and a poor outcome [4]. Resolution of soft-tissue swelling and poor cast application leaves patients at increased risk of fracture displacement [5]. This risk makes early identification of the loss of congruity or (secondary) displacement paramount. Displacement can be identified within the first 2 weeks based upon radiographic imaging. After this period, regular radiographs and clinical assessment are frequently scheduled, based upon existing local trauma protocols for monitoring the fracture-healing process and clinical outcomes ([6,7] and web-based protocols listed at the end of the article).

### Current follow-up protocols

Current protocols that are used both nationally and internationally recommend radiographic assessment at all routine visits (that is, 1, 2, 6 and 12 weeks post-trauma) in order to monitor fracture healing in fractures of the distal radius and ankle. However, it is questionable whether routine imaging following the initial follow-up (that is, post 2-weeks) is justified [8]. Justification for obtaining radiographs beyond the initial follow-up includes documentation of splint application, resident education, assurance that the fracture has not displaced, and medico-legal protection against claims of unintended harm [8]. Three retrospective studies have suggested that routine radiography performed beyond the 2-week follow-up results in longer waiting room visits, unnecessary radiation exposure and increased healthcare costs without providing additional clinical information that impacts clinical decision-making [8-10]. Thus, there is evidence from multiple sources that routine radiographic imaging beyond the 2-week period is clinically redundant. Hence, the current protocol would not appear to be cost effective. In The Netherlands, about 35,000 adults present yearly with fractures of the distal radius and ankle. Based upon the current costs of imaging [11], it is estimated that in the Netherlands approximately €2.9 million could be saved yearly by modifying the current imaging protocol.

### Rationale

We hypothesize that a modification of the current radiographic follow-up protocol towards a protocol with fewer radiographs for patients with distal radius or ankle fractures will lead to significant cost savings without compromising quality of care. The aim of this study is to determine whether a modification of the radiographic follow-up protocol (no standard routine radiographs after 2-week initial follow-up) can be conducted for less direct and indirect healthcare costs, but with no worse outcomes than the current standard of care prescribed for patients with distal radius or ankle fractures.

## Methods/design

### Study design

The WARRIOR-trial (Wrist and Ankle fractures Routine RadIOgraphy Reduction) is a multicenter randomized controlled trial using a non-inferiority design.

The trial includes two study populations: distal radius fracture patients and ankle fracture patients. The interventional effects will be analyzed separately for each type of fracture as independent studies. The same design and research questions apply for both studies.

The study will be conducted in three academic hospitals in The Netherlands (Leiden University Medical Center (LUMC), VU University Medical Center Amsterdam (VUmc) and University Medical Center Groningen(UMCG)). This study is approved by the Medical Ethics Committee LUMC for all participating centers (Number P14.086). The trial is registered in the Dutch Trial Register (Nederlands Trial Register NTR4610, registration date 22 June 2014). Study results will be reported following the Consolidation of Standards of Reporting Trials guidelines [12,13].

### Study population

All patients presenting to the emergency department with a distal radius or ankle fracture and meeting the following criteria are eligible for inclusion: men or women aged 18 years or older; fracture of the distal radius (Orthopaedic Trauma Association Committee for Coding and Classification classification type A-C [14]) or fracture of the ankle (Lauge-Hansen classification: supination-adduction stage II, supination-external rotation stage II-IV, pronation-external rotation stage I-IV [15]); sufficient understanding of the Dutch language in order to independently complete the follow-up questionnaires; written informed consent provided by the patient.

Patients meeting one or more of the following criteria will be excluded: pathological fractures; complicated fractures (Gustilo grade 2 and 3); multi-extremity fractures; psychiatric conditions; unable to complete follow-up (for example, patients living abroad, incarcerated subjects).

### Study procedures

The inclusion and exclusion criteria will be checked for all patients presenting with distal radius or ankle fractures in the emergency department of the participating centers. Eligible patients will be informed of the aims and design of the study and will receive written information.

At the subsequent visit (that is, within the first 2 weeks after the initial visit) the local investigator or research nurse will check the inclusion and exclusion criteria once more, provide additional information, answer any questions regarding the study and obtain written informed consent.

### Randomization

Randomization of patients will be carried out after obtaining written informed consent using an online randomization program (ProMISe, www.clinicalresearch.nl). Randomization will be stratified by center, type of fracture (distal radius or ankle) and treatment (conservative or surgical). Patients will be randomized into the following two groups.

#### Group 1 – usual care

Group 1 will receive usual care according to the current national protocol, indicating clinical follow-up as well as radiographic evaluations in the outpatient clinic at 1, 2, 6, and 12 weeks after trauma.

#### Group 2 – reduced imaging

Group 2 will receive the same clinical evaluations as the usual care group; however, no routine radiographs will be performed beyond the initial 2 weeks. Radiography during follow-up beyond the initial 2 weeks will be allowed if any of the following are present: new trauma to the distal radius or ankle; pain score >6 on the 11-point visual analogue scale (VAS); loss of range of motion (ROM); neurovascular symptoms; at the discretion of the clinician, in which case the indication for radiography is to be recorded in the medical records.

Aftercare apart from radiology will be identical for both study groups and according to the local standards.

At 6 and 12 weeks, 6 months and 1 year, patients will be requested to fill out the questionnaires. The patient can chose between a paper version or a web-based version of the questionnaire. Reminders will be sent when necessary, and attempts will be made to track drop-outs if possible. An overview of follow-up and measurements is provided in Table 1.

**Table 1 Tab1:** **Flowsheet**

	**ER**	**Week 1**	**Week 2**	**Week 6**	**Week 12**	**Week 26**	**Week 52**
Written patient information	X						
Randomization			X				
Baseline characteristics			X				
Radiographs							
Group 1		X*	X*	X	X	○	○
Group 2		X*	X*	○	○	○	○
Visual analogue score			X	X	X	X	X
Function scores (OMAS/AAOS or DASH/PRWHE)			X	X	X	X	X
Quality of Life (SF-36/EQ5D)			X	X	X	X	X
Self-perceived recovery				X	X	X	X
Direct and indirect healthcare costs				X	X	X	X
ROM				X	X		
Complications		X*	X*	X	X	X	X

*Standard Protocol first 2 weeks. X, Measurement collected at each time point; ○, radiography only when clinically indicated; AAOS, American Academy of Orthopaedic Surgeons; DASH, Disabilities of the Arm, Shoulder and Hand Score; EQ5D, EuroQol-5D; ER, emergency room; OMAS, Olerud and Molander Ankle Score; PRWHE, Patient-Rated Wrist and Hand Evaluation; ROM, range of motion; SF-36, Short form-36.

Subjects can leave the study at any time for any reason if they wish to do so without any consequences; patients randomized to Group 2 will revert to the usual care, the care according to the current protocol, after leaving the study.

### Outcomes

#### Primary

The primary outcome is the overall extremity-specific functional status, which for both types of fracture will be measured using Dutch versions of the following questionnaires.

For distal radius fractures the Disabilities of the Arm, Shoulder and Hand Score (DASH) will be used. DASH is the most commonly used questionnaire for measuring upper extremity function [16]. It is a 30-item questionnaire that was designed to evaluate symptoms and physical function in patients with upper extremity disorders. Scoring is done by subtracting 30 points from the sum of the responses. This number is then divided by 1.2 to obtain the score. Missing items are replaced by the mean value of the responses before summing. Scores range from 0 to 100, with 0 reflecting no pain/disability [16-18]. The overall score cannot be calculated if three items or more are missing [16,17,19].

For ankle fractures the Olerud and Molander Ankle Score (OMAS) will be used. The OMAS is a nine-item questionnaire evaluating the functional outcome of the ankle after injury. Scores range from 0 to 100, with 100 reflecting no pain/disability [20].

Secondary outcome measures are: costs; specific function measured with the Patient-Rated Wrist and Hand Evaluation (PRWHE) for the wrist fractures and the American Academy of Orthopaedic Surgeons (AAOS) foot and ankle questionnaire for ankle fractures; pain intensity at rest; health-related quality of life measured with the Short Form-36 (SF-36) questionnaire and the EuroQol-5D (EQ5D) questionnaire; self-perceived recovery; ROM; and complications.

Costs will be investigated using a healthcare utilization questionnaire. The costs of healthcare consumption include, for example, costs for consulting the general practitioner, company doctor and/or physiotherapist, costs of medication and hospitalization, and costs of absence from work associated with the fracture of the distal radius or ankle.

The PRWHE is a 15-item (five pain and 10 disability items) questionnaire that rates pain and disability of the wrist in functional activities [18]. Scoring is done by adding up the sum of the five pain items and the sum of the 10 disability items, and dividing by two. Missing items are replaced by the mean score of the subscale. Scores range from 0 to 100, with 0 reflecting no pain/disability [16-18].

The AAOS foot and ankle questionnaire is a commonly used 25-item questionnaire that combines items on pain, function, stiffness and swelling, and allows assessment of the patient’s perception of the condition of the ankle/foot and the treatment progress [21,22]. Scoring is done by an online worksheet that can be found at http://www.aaos.org/research/outcomes/outcomes_lower.asp.

Pain intensity at rest is measured using a continues VAS, where 0 reflects no pain and 10 the worst possible pain.

The SF-36 is a 36-item questionnaire about health status recorded by the patient. The items are subdivided into eight health concepts. Combining these concepts leads to two health scales: a physical health scale and a mental health scale [23,24]. The scores range from 0 to 100 points, with higher scores reflecting better function. The derived score has to be converted to a norm-based score in order to make it possible to compare the score with the norms for the general population of the United States (1998), in which each scale was scored to have the same average of 50 points and the same standard deviation of 10 points [25,26].

The EQ5D is a five-item questionnaire to assess health-related quality of life. The questionnaire measures the ability to walk, the ability to perform daily activities, depression, anxiety and pain on a three-point scale. These scores are combined to describe the health status of the patient, which can be linked to a preference (utility) for the health status obtained from the general population [27,28].

The self-perceived recovery is measured on a five-point Likert-scale.

The ROM of the wrist or ankle joint will be measured during the outpatient clinic visits at weeks 6 and 12 after trauma. The ROM in the wrist will be tested by measuring the palmar flexion, dorsal extension, pronation and supination. The ROM in the ankle will be tested by measuring the flexion, plantar flexion, inversion and eversion.

Complications that will be registered include infection, nonunion, malunion and implant failure. These will be recorded from the medical charts by the investigator.

Potentially confounding variables, such as age, gender and socio-demographic characteristics will be registered.

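### The PRWHE scoring rule, read literally, cannot produce the 0-100 range stated beside it

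*Protocol article*

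**What the plan says.** The PRWHE is described in the Protocol article under Methods/design, Outcomes, in the text that follows the primary outcomes. It is listed there as a secondary outcome: "specific function measured with the Patient-Rated Wrist and Hand Evaluation (PRWHE) for the wrist fractures". Three statements about its score stand together:

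- Composition: "The PRWHE is a 15-item (five pain and 10 disability items) questionnaire".
- Rule: "adding up the sum of the five pain items and the sum of the 10 disability items, and dividing by two".
- Range, and how gaps are filled: "Missing items are replaced by the mean score of the subscale. Scores range from 0 to 100, with 0 reflecting no pain/disability".

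The article does not give the response range of a single item, and it does not say what share of the total each subscale should carry. Table 1 schedules the function scores at weeks 2, 6, 12, 26 and 52. The planned wrist sample is 385 patients.

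**The concern.** In the scoring sentence the division comes after the addition and is set off by a comma. Taken as a formula, it halves the total of both subscales. That formula and the 0-100 range are given for the same 15 items in the same paragraph, and they do not appear to fit together.

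The consequence would be more than a change of units. Halving the whole sum, rather than the disability part alone, changes how much pain counts relative to disability. Two patients with the same literal total can have different totals under a rule that does reach 100, so the fault could not be repaired later from stored totals. The item data or the subscale sums would be needed.

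**Working it through.** **Inputs from the article:** five pain items, 10 disability items, the rule as worded, and the range 0 to 100. **Not in the article:** the item range. I let every item run from 0 to k and vary k. The items must start at 0, because a total of 0 is stated to be attainable; items scored 1-10 would give a literal minimum of 15/2 = 7.5.

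Let P be the pain sum (maximum 5k) and D the disability sum (maximum 10k).

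**1. Try to reproduce the stated range with the literal rule, (P + D)/2.**

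Maximum = (5k + 10k)/2 = 7.5k.

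| k | Maximum |
|---|---|
| 5 | 37.5 |
| 10 | 75 |
| 13 | 97.5 |
| 14 | 105 |

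A maximum of 100 needs k = 100/7.5 = 13.33. No whole-number scale shared by all 15 items gives this, so the stated range is not reproduced. This result does not depend on assuming 0-10 items.

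**2. Try the alternative reading, P + D/2.**

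Maximum = 5k + 10k/2 = 10k, which is 100 at k = 10. The stated range is reproduced with 0-10 items.

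**3. Compare the two readings.**

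(P + D/2) − (P + D)/2 = P/2.

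The literal score is lower by half the pain sum. For a between-arm difference, the literal rule gives ΔP/2 + ΔD/2 and the alternative gives ΔP + ΔD/2. The pain part is halved and the disability part is the same.

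Examples with 0-10 items (assumed):

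| P | D | (P + D)/2 | P + D/2 |
|---|---|---|---|
| 40 | 40 | 40 | 60 |
| 20 | 60 | 40 | 50 |
| 30 | 40 | 35 | 50 |
| 0 | 100 | 50 | 50 |

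The first two rows share a literal score of 40 but differ by 10 points under the alternative, so no constant multiplier converts one score into the other. The last row shows that a patient without pain scores the same either way.

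**4. Control: the DASH rule in the same section.**

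The article says: "Scoring is done by subtracting 30 points from the sum of the responses. This number is then divided by 1.2 to obtain the score". With 30 items scored 1-5 (assumed), this gives (30 − 30)/1.2 = 0 and (150 − 30)/1.2 = 100, which matches its stated range. The DASH rule works when read literally; the PRWHE rule does not.

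**5. Other ways to reach 100.**

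- Different maxima for the two item types would work if 5a + 10b = 200, for example pain items 0-20 and disability items 0-10. Nothing in the article suggests this.
- With 0-10 items, dividing the whole sum by 1.5 gives 150/1.5 = 100. Pain then keeps a share of 5/15, one third.

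**The case against.** The strongest reply is that the sentence is only loosely worded. The closing words about division can be attached to the disability sum alone, and a reader who takes items as 0-10 is led to that reading by the range given two sentences later. On this view it is a drafting slip in a condensed article, and nothing shows that the database will be scored by the literal wording. This stands as far as it goes: the document cannot show how scoring will be done, so the harm is conditional on the rule being applied as written. It does not remove the conflict. The article chose to give a formula, the formula read in its natural order fails, and nothing elsewhere corrects it.

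Several stronger readings are tempting, and the documents do not support them:

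- *Pain should carry half the weight.* The article states no intended weight. One half follows only from the repair in step 2; the division by 1.5 in step 5 would restore the range and leave pain at one third.
- *The maximum is 75.* This is so only if items run 0-10.
- *Every patient's score is wrong.* Patients with a pain sum of zero score the same under both readings.
- *Results could not be compared with other PRWHE studies.* The article gives no external scoring standard and no other PRWHE results, so this cannot be judged from it.
- *The trial would be tilted towards non-inferiority.* The same rule would apply in both arms, and the article sets no margin for the PRWHE. The spread of the scores would change along with the differences, so the effect on any test cannot be worked out from what is given.

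**Conclusion.** The point holds as an internal contradiction: the literal rule and the 0-100 range cannot both be right for any whole-number item scale common to the 15 items. That conclusion needs only the item counts and a shared scale starting at 0.

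The size of the consequence rests on two further assumptions: items of 0-10, and the pain sum plus half the disability sum as the intended total. On those, the literal maximum is 75 instead of 100, each score falls by half its pain sum (up to 25 points when P = 50), and a between-arm pain difference is halved in points.

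The reach is limited. The PRWHE is a secondary outcome in wrist patients only. The DASH and OMAS primary outcomes, the 9-point margin and the sample size do not use it. It is worth correcting before scoring because the correction is cheap and the fault cannot be undone from totals alone.

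**What to change.** State the item range and reconcile the rule with the score range before any PRWHE data are scored. One wording that agrees with 0-100 is: *PRWHE total = sum of the five pain items + (sum of the ten disability items divided by two); items scored 0-10; range 0-100.* Confirm it against the instrument's own scoring instructions before adopting it, because the article alone does not settle which repair is intended. Then check that the scoring syntax matches, and keep the item-level data or both subscale sums in the database.

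The cost is one sentence in the protocol or analysis plan and one line of syntax. No change to the design, the sample size or data collection is needed.

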### Statistical analysis

Data will be analyzed using the IBM SPSS version 20 or higher (Armonk, NY: IBM Corp.). Characteristics of the patients in the treatment groups will be presented using descriptive statistics (mean ± standard deviation, median (range) or proportion) to assess if balanced groups were obtained after randomization.

The data analysis will be conducted according to the intention-to-treat principle, with a normal approximation for all questionnaires at 6, 12, 26 and 52 weeks for both types of fractures. For analysis of the primary study outcome, linear and generalized multilevel analyses will be used accounting for dependency within hospitals, clinicians and patients over time (four-level model). This means, among other things, that the data are to be analyzed longitudinally and, thus, the follow-up measurements are to be incorporated in the analyses. Results will be expressed as confidence intervals and these will be subsequently compared to the margin of non-inferiority in order to make inferences about the non-inferiority of the new intervention strategy. In addition to crude analyses, all analyses will also be adjusted for pre-defined prognostic factors, such as age, gender and fracture type. In a secondary analysis, a per-protocol analysis will be conducted which will account for ‘contamination’, meaning those randomized to the intervention group but nonetheless requiring follow-up imaging not allowed in the original treatment design (because there was a clinical indication for imaging).

The secondary clinical outcome measures of quality of life and pain will be analyzed in the same way as the primary outcome measure. The secondary outcome measures of ROM and complications will be compared between the ‘usual care’ group and the ‘reduced images’ group over time.

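### The planned complication comparison is open to detection bias favouring reduced imaging, because only usual care has routine films after week 2

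*Protocol article*

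**What the plan says.** All references are to the protocol article.

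- **Which complications.** Outcomes: "Complications that will be registered include infection, nonunion, malunion and implant failure". The source is the chart: "These will be recorded from the medical charts by the investigator". Table 1 collects complications through week 52.
- **Imaging in usual care.** Group 1 has "radiographic evaluations in the outpatient clinic at 1, 2, 6, and 12 weeks after trauma".
- **Imaging in the reduced arm.** In Group 2, "no routine radiographs will be performed beyond the initial 2 weeks". Exceptions are allowed for new trauma, high pain, lost range of motion or neurovascular symptoms, or "at the discretion of the clinician, in which case the indication for radiography is to be recorded in the medical records".
- **Later visits.** At weeks 26 and 52, Table 1 gives both groups the same entry: "radiography only when clinically indicated".
- **Purpose of the later films.** The abstract says that after the first two weeks "routine radiographs are scheduled for monitoring the bone-healing process".
- **Analysis.** Statistical analysis: "The secondary outcome measures of ROM and complications will be compared between the" two groups over time. Nothing is said there about unequal ascertainment.

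**The concern.** The intervention changes how often clinicians look for three of the four complications. A nonunion, malunion or implant failure without symptoms can enter a Group 1 chart because a scheduled film showed it. The same event in Group 2 may never be seen. The chart count then depends on the arm as well as on what happened to the fracture.

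The direction is predictable: Group 2 looks better than it is. The trial's stated aim (Rationale) is lower cost without worse outcomes, so readers will look to the complication table for reassurance on safety. Fewer recorded events in Group 2 could partly reflect less imaging, and a true excess in Group 2 could be reduced or hidden.

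**Working it through.** **Step 1. Compare scheduled imaging by arm (Group 1, Group 2, Table 1).**

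| Time | Group 1 | Group 2 |
|---|---|---|
| Weeks 1, 2 | routine | routine |
| Weeks 6, 12 | routine | on indication |
| Weeks 26, 52 | on indication | on indication |

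No scheduled film after week 2 is common to both arms.

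**Step 2. Ask which components depend on films.** The article gives no definitions. That nonunion, malunion and implant failure are established largely on radiographs is general clinical knowledge. The article's own account of the later films, as monitoring of bone healing, is consistent with it. Infection is largely a clinical diagnosis. DASH and OMAS are questionnaires and do not depend on films.

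**Step 3. Ask which events are affected.** Symptomatic events can be imaged in either arm. Events that stay silent can be found routinely in Group 1 only. The asymmetry therefore concerns mainly silent events.

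**Step 4. Illustrate the size.** The article states no complication rate and no detection rate, so there is no figure of its own to reproduce. All inputs here are assumptions and refer to the film-dependent components only.

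Let p be the true rate, equal in both arms, and s1 and s2 the detection probabilities in Groups 1 and 2. Then:

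- recorded rate = p × s
- spurious difference (Group 2 − Group 1) = p × (s2 − s1)
- recorded risk ratio = s2 / s1

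With s1 = 1.00, the spurious difference in percentage points is:

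| p | s2 = 0.90 | s2 = 0.75 | s2 = 0.50 |
|---|---|---|---|
| 2% | −0.2 | −0.5 | −1.0 |
| 5% | −0.5 | −1.25 | −2.5 |
| 10% | −1.0 | −2.5 | −5.0 |
| Recorded risk ratio | 0.90 | 0.75 | 0.50 |

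With equal detection (0.95 in both arms) the difference is 0.

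**Step 5. Express one case as counts.** The Sample size section gives 350 wrist and 284 ankle patients before the allowance for loss to follow-up. The allocation ratio is not stated; 1:1 is assumed, giving 175 and 142 per arm. At p = 5% and s2 = 0.75:

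- wrist: 175 × 0.05 = 8.8 recorded in Group 1, and 175 × 0.0375 = 6.6 in Group 2
- ankle: 142 × 0.05 = 7.1 and 142 × 0.0375 = 5.3

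**Step 6. Masking.** With unequal true rates, the recorded risk ratio is the true ratio × s2/s1. At s2/s1 = 0.75, a true ratio of 1/0.75 = 1.33 against Group 2 would be recorded as 1.00.

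**The case against.** Several points on the other side have force.

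- **Safeguards.** Group 2 has the same clinical visits, and range of motion is measured in both arms at weeks 6 and 12, the visits at which Group 1 is filmed. Indicated films are allowed. Follow-up runs to week 52 with identical imaging rules at weeks 26 and 52, so an event missed early can still be recorded if it becomes symptomatic. This stands. It confines the bias mainly to events that stay silent, but does not remove it.
- **Consequence.** Non-inferiority is judged on DASH and OMAS against a 9-point margin. Pain, quality of life, self-perceived recovery and range of motion are scheduled alike in both arms. This stands too. A reader might infer that the trial's main conclusion is compromised; the article does not support that.
- **Size.** A reader might infer a large artefact. For example, 10% incidence with 95% v 30–60% detection gives 9.5% v 3.0–6.0%, a gap of 3.5–6.5 points. No figure in the article supports those inputs, or the milder ones used above.
- **Weeks 1 and 2.** A reader might infer that events from before randomization contaminate the comparison, because Table 1 lists complications at those visits. The entries carry an asterisk marking them as standard protocol, and nothing says that they enter the between-arm analysis.
- **Condensation.** Complication definitions and adjudication may be in the full protocol or analysis plan, and their absence here is no fault. However, the asymmetric imaging, the chart source and the between-arm comparison are all fixed in the article itself.
- **Recorded indication.** The article requires the indication to be noted for discretionary films in Group 2. That does not capture how each complication came to light in both arms.

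**Conclusion.** The concern holds for one secondary outcome. Followed as written, the plan compares nonunion, malunion and implant failure between arms that are searched differently at weeks 6 and 12, and the resulting bias favours reduced imaging. It acts mainly through events that stay clinically silent. Infection and the patient-reported primary outcome are not materially affected.

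The direction follows from the article, together with the clinical premise that these three diagnoses rest largely on films. The size does not follow from the article: 0.2–5.0 percentage points is an illustration under assumed true rates of 2–10% and Group 2 detection of 50–90% against 100%. It would be wrong to conclude that any shortfall of events in Group 2 must be an artefact; as planned, the data could not tell the two explanations apart.

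**What to change.** 1. For each complication arising after randomization, record in the chart abstraction how it was first detected: by a symptom, clinical sign or unscheduled visit, or only on a routine week-6 or week-12 film. Group 1 patients are examined and filmed at the same visit, so the coding should rest on whether a symptom or clinical finding was noted, not on whether the film was scheduled.
2. Base the between-arm comparison on infection and on nonunion, malunion or implant failure first prompted by symptoms or clinical findings, whatever treatment followed.
3. Tabulate separately, as descriptive data, the events first found only on a routine film. Include those that then led to a treatment change or re-intervention. Treatment cannot serve as the criterion for the main comparison, because a silent finding on a Group 1 film can itself prompt treatment.
4. If such an event later becomes symptomatic, count it in the clinical comparison from that time.

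The change needs no additional imaging. It costs one abstraction field, a few sentences of analysis text, and fewer countable events, so a somewhat wider interval. It reduces the bias without removing it entirely: a silent Group 1 event treated before symptoms appear leaves the clinical comparison, which is why the descriptive table should be reported beside it.
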